### Ethics

The study has been approved by the Health Research Authority (HRA) as a research study, following review at the South-East Coast—Surrey Research Ethics Committee (REC reference: 16/LO/1827; IRAS project ID: 215,928). All hospitals provide Caldicott Guardian approval in addition to confirmation of capacity and capability in accordance with usual HRA requirements.

### Participants

All NHS hospitals which undertake any of the included procedures are eligible to participate. Hospitals are approached via the Royal College of Anaesthetists and its Health Services Research Centre, and via the National Institute for Health Research’s portfolio system. Patients aged 18 years or older undergoing planned major surgery (as defined by a list of index procedures requiring inpatient stay) will be eligible for recruitment and patient consent will be sought pre-operatively. Patient consent is required as the study seeks additional data to that collected as part of routine care (specifically the patient-reported outcome data). The consenting process is undertaken by staff locally trained and approved. The participant information provides detail on how data are collected, the request for patient reported data, and the linkage of hospital data with external databases (see below, dataset).

Hospitals may choose to recruit patients from all specialties or specify particular specialties where they wish to focus at local level. Each hospital is offered the opportunity to either approach all eligible patients for consent, or all patients within a particular specialty or plan to recruit between one and five patients per week, approaching patients for written consent based on a random sampling strategy. This will involve an eight-day rolling sampling cycle (i.e. for week one the first five patients starting on Monday morning, followed by the first five patients starting from Tuesday in week two, et cetera). If any of the first five patients approached decline to consent, then consecutive patients will be approached for consent until the target recruitment number has been achieved. Patients can choose to be withdrawn from the study at any time.

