### Limitations

The requirement for patient consent means that the sample may be biased. While this is of less importance for process measures which will be used to evaluate care quality, it is relevant when considering outcomes. We will mitigate this risk through comparison of the PQIP population to the total sample of patients undergoing PQIP included procedures using Hospital Episode Statistics (HES) data. This will enable us to undertake sensitivity analyses which will demonstrate what (if any) biases there are in our sampling.Similarly, our ambition to enable as many hospitals as possible to participate irrespective of local resourcing, means that some hospitals will attempt to recruit all patients who are potentially eligible, and some only a sample. We will again try to mitigate this risk through encouraging hospitals to recruit a random sample of patients and will compare the PQIP sample against the HES-defined population at local level as well.

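### The sampling option called random is a fixed systematic consecutive rule and, where planned lists run on weekdays only, it favours Monday patients

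*Protocol article*

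**What the plan says.** The Participants section gives hospitals three options. Two involve no sampling: "Each hospital is offered the opportunity to either approach all eligible patients for consent, or all patients within a particular specialty". The third is to "plan to recruit between one and five patients per week, approaching patients for written consent based on a random sampling strategy".

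The same section then defines the third option: "This will involve an eight-day rolling sampling cycle (i.e. for week one the first five patients starting on Monday morning". One week later the start shifts to Tuesday, and later starts continue to shift in the same way. If any of these patients decline, "consecutive patients will be approached for consent until the target recruitment number has been achieved".

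The Limitations section acknowledges that some hospitals will recruit only a sample. It offers two mitigations: "encouraging hospitals to recruit a random sample of patients", and a comparison with the HES-defined population at local level. The section on evaluating sample validity (RQ8) requires that sampling for outcomes be robust and not give biased estimates, and it sets out the HES comparison. The Discussion reports that random sampling proved largely infeasible and that most sites adopted convenience sampling.

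**The concern.** The label and the definition do not match. The start day, the patients taken from that start and the replacements for refusals are all fixed by the calendar and by the order of patients. No step involves chance.

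Two consequences follow for a site that applies the rule exactly:

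- **Weekday.** An eight-day step passes through all seven days of the week, but eligibility is limited to planned surgery. Where planned lists run on weekdays only, a weekend start has no patients of its own and passes to the following Monday.
- **Order.** Where a day has more eligible patients than the quota, those later in the sequence enter mainly when earlier ones decline.

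At stake is whether this option can serve as the mitigation for partial recruitment that the Limitations section describes, and whether a site's feedback rates describe its whole week. The difference would matter if case mix or care varies by weekday or by order. The article gives no data on that.

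**Working it through.** **Inputs from the Participants section**

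- Step between starts: 8 days, first start on a Monday.
- Quota T: 1 to 5 patients per start (the article's example uses five).
- Patients are taken in order from the start.

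**Assumptions not in the documents**

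- No planned lists on Saturday or Sunday; a weekend start passes to the next Monday.
- D eligible patients on each weekday, so each weekday should supply 1/5 = 20%.
- No refusals.

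**Step 1: reproduce the stated sequence.** Starts fall on day 8k, for k = 0, 1, 2 and so on, with Monday of week one as day 0. Days 0, 8, 16, 24, 32, 40 and 48 are Monday, Tuesday, Wednesday, Thursday, Friday, Saturday and Sunday. Day 56 is a Monday again. This matches the article's Monday-then-Tuesday example.

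**Step 2: effective starts.** The Saturday start (day 40) passes to Monday, day 42. The Sunday start (day 48) passes to Monday, day 49. Of every seven starts, Monday receives 1 + 2 = 3 and each other weekday receives 1. These Mondays are a week apart, so no patient is counted twice.

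**Step 3: one day fills the quota (D ≥ T).** Monday's share is 3T/7T = 3/7 = 42.9%, which is 42.9/20 = 2.1 times its fair share. Each other weekday has 1/7 = 14.3%, or 14.3/20 = 0.71 times. With T = 1 this holds at every D of one or more.

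**Step 4: quota of five with smaller lists.** Seven starts give 7 × 5 = 35 patients.

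- D = 4: each start takes 4 patients, then 1 on the next weekday. Monday has 3×4 from its own starts plus 1 carried over from the Friday start = 13.
- D = 3: each start takes 3, then 2. Monday has 3×3 + 2 = 11. Tuesday has 3×2 + 3 = 9.
- D = 2: each start takes 2, 2, then 1. Monday has 3×2 + 2 (Friday start) + 1 (Thursday start) = 9. Tuesday has 3×2 + 2 + 1 = 9.
- D = 1: each start takes one patient from every weekday. Monday has 7.

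| Eligible per day | Mon | Tue | Wed | Thu | Fri |
|---|---|---|---|---|---|
| 5 or more | 42.9% | 14.3% | 14.3% | 14.3% | 14.3% |
| 4 | 37.1% | 20.0% | 14.3% | 14.3% | 14.3% |
| 3 | 31.4% | 25.7% | 14.3% | 14.3% | 14.3% |
| 2 | 25.7% | 25.7% | 20.0% | 14.3% | 14.3% |
| 1 | 20.0% | 20.0% | 20.0% | 20.0% | 20.0% |

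**Step 5: drop the weekday-only assumption.** With equal lists on all seven days, each day supplies 1/7 = 14.3% and there is no weekday imbalance. Selection by order remains: at D = 10 and T = 5, patients in positions 6 to 10 are not reached unless someone declines.

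**Step 6: check the remedy.** Start on every sixth operating day of a five-day week: Monday, the next Tuesday, and so on to Friday, then the Monday ten calendar days later. Each weekday then has one start in five. A quota of up to five is filled before the next start, even at D = 1. Enumeration at T = 1, 3 and 5 and at D = 1, 2, 3, 4, 5 and 10 gives 20.0% for every weekday. The spacing matters. If a Friday start is followed by a start on the very next Monday, the two runs overlap when a day does not fill the quota. At T = 5 and D = 2 the Monday-to-Friday shares become 12%, 16%, 24%, 28% and 20%.

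**The case against.** **The Monday figure rests on facts outside the article.** This is correct. Weekday-only lists, equal caseload and no refusals are assumptions, and the article does not say what happens when a start falls on a day without lists. A rotation confined to Monday to Friday would remove the systematic Monday excess, but it would not be the eight-day cycle that is written. The labelling point needs none of these assumptions.

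**HES is the reference, not this sample.** This stands. A reader might infer that the article treats the sampling option as an unbiased benchmark. It does not: the Limitations section offers it only as mitigation, and the HES population is the comparator locally and nationally. That comparison may detect some bias, although weekday and order are not among the characteristics given as examples.

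**Later patients are not shut out.** This stands too. The replacement rule brings them in after refusals. Nor does the article say that *first* means first on a theatre list. Patients may be approached by mail, in clinic or on the day of surgery, so selection by list position is an inference.

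**No harm is shown.** A reader might infer that PQIP's reported rates are distorted by Monday patients. The documents give no effect of weekday or order on any outcome or process measure. Risk adjustment includes operation type, and the article holds that non-random sampling matters less for process measures.

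**The rule is largely superseded.** Most sites have moved to convenience sampling, which limits the reach. The Participants section still states the rule as the plan, however, and the number of sites still using it is not given.

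**Conclusion.** The point holds as a minor one. Without any assumption, the option labelled random is systematic consecutive sampling, and followed exactly it does not deliver the random sample that the Limitations section offers as mitigation.

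Under the stated assumptions, Monday's share lies between 20% and 42.9%, depending on how daily caseload compares with the quota. Weekend lists would reduce the excess. These are shares of the sample, not biases in outcome rates, and the documents do not support a claim about the latter. Only sites that still use the sampling option are affected.

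**What to change.** 1. In the Participants section and the site instructions, rotate the start over the site's actual operating days only. State the step in operating days: one more than the number of operating days in the week, so six for a Monday-to-Friday site. This gives 20% per weekday under equal caseload.
2. In the Participants and Limitations sections, describe the scheme as systematic consecutive sampling. Keep the word random only if a pre-generated random start is actually used.
3. For patients already recruited under the rule, reporting or weighting by weekday of surgery is an optional sensitivity analysis. It cannot correct selection by order, because patients who were never reached leave no data to weight.

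Cost: a small change to site instructions and a start table, for the remaining sampling sites only. Starts become slightly less frequent at a five-day site: five in six weeks (0.83 a week) against seven in eight weeks (0.88 a week). A random starting patient, if chosen, would mean checking the whole day's eligible patients, which should be weighed against the infeasibility already reported.

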#### Sample size

Target recruitment is 70,000 patients. It is expected that this will take at least 5 years to achieve. The long observation period will facilitate the study of how data collection and feedback impacts upon patient outcomes over time.

### Dataset

The dataset has been informed using the best available evidence. The primary outcome is the presence of any POMS-defined morbidity on postoperative day seven. Secondary outcomes will include: POMS-defined major morbidity (Wong et al. 2017); complications graded according to the Clavien-Dindo classification; failure to rescue (FTR); resource utilisation (critical care admission (planned/unplanned); critical care length of stay, hospital length of stay, hospital readmission within 30 days of index procedure); mortality at 90 days; days alive and out of hospital (Moonesinghe et al. 2017)censored at 30 days, 60 days, 90 days and one year postoperatively; disability-free survival at one year; change in patient reported health related quality of life (HRQOL) between baseline and 6 and 12 months after surgery; the responses to the “Ask2Questions” brief questionnaire about complex pain (Faculty of Pain Medicine, London, UK 2022). The choice of outcome measures has been based on formal validation studies (Grocott et al. 2007; Dawson et al. 2001; Shulman et al. 2015)and expert consensus (Clavien et al. 2009; Hutchings et al. 2012; Hutchings et al. 2013; Hutchings et al. 2014; Neuburger et al. 2011; Neuburger et al. 2012; Neuburger et al. 2013; Neuburger et al. 2013). To calculate FTR, we will follow previously described methodology, but using the presence of a Clavien-Dindo grade II or above complication as our definition of postoperative complications (Silber et al. 1992; Silber et al. 2007). Given the changes in how perioperative care is coordinated (e.g. enhanced recovery programmes aiming for early discharge) we will also use different endpoints for mortality to compare and contrast different approaches to how FTR could be measured in the modern era – for example, inpatient death vs. 30-day mortality vs. 60-day mortality). Candidate variables for risk adjustment have been selected from the results of a systematic review, and subsequent original research (Moonesinghe et al. 2013; Protopapa et al. 2014; Canet et al. 2010). These include: physiological measurements (e.g. blood pressure); long-term conditions and their control (e.g. diabetes and HbA1C and heart failure / New Your Heart Association grade) and laboratory results (e.g. haematological and biochemistry assays), as well as more novel measures such as deprivation index. Process measures have been informed by systematic review (Chazapis et al. 2018) and Delphi consensus process. An expert panel (the Clinical Reference Group) of stakeholders from different medical and surgical specialties provided further input to refine the long-list of potential measures. These include measures of staffing (level of seniority of surgeons and anaesthetists involved in care delivery), intraoperative anaesthesia and surgical practice, and enhanced recovery metrics before and after surgery. In addition to prospectively collected data, we will also link patient-level data with NHS Digital Hospital Episode Statistics and the Office of National Statistics mortality register. We will also consider patient-level linkage with other registries such as the National Cancer Registry, the Intensive Care National Audit and Research Centre’s Case-Mix Programme and relevant National Clinical Audits, in order to provide a comprehensive dataset at lowest local data collection burden.

#### Study flow

Patients are approached for participation either by mail, at the preoperative assessment clinic or on the day of surgery. A minimum of 1 h is allowed for patients to consider the information on the participant information sheet before they are asked whether they wish to consent. At the time of consent, patients are asked to indicate whether they wish their longer-term follow-up to be by email or telephone. Following consent, the patient is asked to complete baseline demographic and HRQOL data. On the day of surgery, clinical teams or research staff complete preoperative, intraoperative and recovery room data. Further objective data capture occurs on day 2 or 3 (the Drinking Eating and Mobilising process measure (Levy et al. 2016)), day 7 (the Post-Operative Morbidity Survey (POMS) (Grocott et al. 2007)) and at hospital discharge (the Clavien-Dindo complications grading scale (Clavien et al. 2009; Dindo et al. 2004), and information about the length of stay and post-discharge destination of the patient. In addition, patients are asked to complete a patient satisfaction with anaesthesia questionnaire (Bauer et al. 2001; Walker et al. 2016)within 24 h of surgery, a quality of recovery questionnaire at baseline (at the time of consenting to participate in PQIP) and postoperative day 3 (Stark et al. 2013; Chazapis et al. 2016), and longer-term HRQOL and disability-assessment questionnaires at baseline, 6 and 12 months after surgery (Dawson et al. 2001; Shulman et al. 2015).

#### Loss to follow-up

We are conscious that with a large pragmatic study of this nature without substantial funding but with multiple follow-up points and hospitals participating, that there is the potential for significant loss to follow-up. We have considered this as follows:

Inpatient morbidity and complication follow-up rates are predicted to be high, as they are collected in-hospital. We have created logic checks within our online data entry tool to enable us to differentiate between missing data and negative responses. Hospitals with large amounts of missing data will be contacted and offered support.

Mortality follow-up rates are likely to be high, as availability of the information does not depend on patients being contactable or willing to respond to a questionnaire (through linkage with NHS databases). There will be a small number of patients for whom data linkage is not possible (for example if they have left the NHS) but we will receive information about this type of loss to follow-up from NHS Digital.

For longer-term patient-reported outcomes, we will take measures to maximise response rates, for example through multiple reminder letters & phone calls. Additionally, and where required and appropriate, we will conduct sensitivity analyses to understand if there are any important differences between responders and non-responders and to assess for potential biases.

#### Co-enrolment

There is no barrier to PQIP patients being co-enrolled into other studies. We actively seek collaboration with other researchers to facilitate co-enrolment with other studies while paying attention to the need to minimise redundant data collection and data collection fatigue of patients and investigators.

#### Data sharing

Local data can be exported by approved local investigators at each hospital at any time. We will invite PQIP collaborators to apply for multi-centre data to undertake their own secondary analyses which are outside our initial analysis plans. These applications will be reviewed by the PQIP project team and assistance offered for analysis and interpretation, subject to capacity. Applications for access to PQIP data by non-PQIP collaborators will be considered when the study and the planned analyses are completed. Fully anonymised datasets will be made available on data sharing resources once the study and all follow-up is complete.

## Analysis plan

### Descriptive statistics (RQ1, RQ2)

Descriptive statistics will be used to describe the basic demographics of participants. We will report process measures of engagement with PQIP (case-ascertainment rates, data completion) and compliance with processes of care at local and national level. (RQ1) Both unadjusted and adjusted outcomes will be reported (see inferential statistics for details of risk adjustment). (RQ2) All hospital level data will be presented anonymously.

### Missing data

For each statistical analysis, we will document the number and rate of missing observations on all variables involved. For each statistical model, we will assess the likely process that lead to missing observations, and whether data are likely to be missing at random (MAR) or missing not at random (MNAR). This assessment will inform a decision about the appropriate method of analysis. For example, multiple imputation or imputation of normal values may be considered for predictors in statistical models, depending on the likely process of missingness. Patients who are missing outcome data will be omitted from the relevant analysis; sensitivity analyses will be conducted to evaluate differences between patients with and without missing outcome data.

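### The blanket rule of omitting patients with missing outcomes should not apply to one-year disability-free survival, where it gives a biased estimate even if questionnaire non-response among survivors is random

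*Protocol article*

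**What the plan says.** The rule is in the Missing data section of the analysis plan: "Patients who are missing outcome data will be omitted from the relevant analysis". That section first says that the likely missingness process will be assessed for each model and will guide the choice of method. Its examples of imputation concern predictors. It adds sensitivity analyses that compare patients with and without outcome data.

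The outcome in question is in the Dataset section, among the secondary outcomes: "disability-free survival at one year". Its two parts come from different sources:

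- **Disability.** Study flow describes "longer-term HRQOL and disability-assessment questionnaires at baseline, 6 and 12 months after surgery", so one-year disability is known only for patients who answer at 12 months.
- **Death.** Loss to follow-up explains that deaths come from linkage with NHS databases, so that "availability of the information does not depend on patients being contactable or willing to respond to a questionnaire". The exception is limited: "There will be a small number of patients for whom data linkage is not possible".

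The same section warns that "there is the potential for significant loss to follow-up" and, for patient-reported outcomes, plans reminders and, where required, comparisons of responders with non-responders.

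**The concern.** A patient known from linkage to have died has a known result for disability-free survival: failure. A living patient who does not return the questionnaire has no result. Under the omission rule the first stays in the analysis and the second leaves it. Inclusion then depends on the outcome itself. Deaths are over-represented, and the composite is not missing completely at random even when questionnaire non-response among survivors is.

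The temporal and between-hospital section (RQ3) plans comparisons of every primary and secondary outcome over time and between hospitals. The bias depends on the response rate, so hospitals with the same mortality and disability but different questionnaire return would show different disability-free survival. A drift in response over calendar time would look like a trend. Adjustment for case-mix is not designed to remove this, because a hospital's response rate is not case-mix. Disability-free survival is also named in the section on relationships between outcomes (RQ5).

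**Working it through.** The article states no figure for disability-free survival, one-year mortality, disability or response, so there is no figure to reproduce. Its only mortality range is for 30 days, 0.6% to 4% (Introduction).

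**Inputs, all assumed**

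- d = one-year mortality: 5%, with 2% and 10% as a range
- s = proportion of survivors free of disability: 80%
- r = questionnaire response among survivors: 80%, 60% or 40%, independent of disability
- every death is linked (relaxed below)

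**Formulas**

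- True value: (1 − d) × s
- Omission rule, deaths kept: (1 − d) × r × s / [d + (1 − d) × r]
- Share of deaths among analysed patients: d / [d + (1 − d) × r]
- True value minus estimate: (1 − d) × s × d × (1 − r) / [d + (1 − d) × r], which is positive whenever d > 0 and r < 1

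**Results at d = 5%, s = 80%.** The true value is 0.95 × 0.80 = 76.0%.

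| Non-response | Calculation | Estimate | Bias (points) | Share of deaths |
|---|---|---|---|---|
| 20% | 0.608 / 0.810 | 75.1% | −0.9 | 6.2% |
| 40% | 0.456 / 0.620 | 73.5% | −2.5 | 8.1% |
| 60% | 0.304 / 0.430 | 70.7% | −5.3 | 11.6% |

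**Range of mortality**

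- d = 2%, 20% non-response: 0.6272 / 0.804 = 78.0% against 78.4%, a bias of −0.4 points.
- d = 2%, 40% non-response: 77.4% against 78.4%, −1.0 point.
- d = 10%, 40% non-response: 67.5% against 72.0%, −4.5 points.
- d = 10%, 60% non-response: 0.288 / 0.460 = 62.6% against 72.0%, −9.4 points.

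**Incomplete linkage.** If 98% of deaths are captured (assumed), then at d = 5% and 40% non-response the estimate is 0.456 / (0.049 + 0.570) = 73.7%, still 2.3 points low. The bias vanishes only if everyone responds, nobody dies, or deaths go missing at the same rate as questionnaires.

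**Two hospitals, illustrative.** Both have a true value of 76.0%. With 20% and 60% non-response they would show 75.1% and 70.7%, a gap of 4.4 points that reflects response alone.

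**Other reading of the rule.** If everyone without a 12-month questionnaire is dropped, deaths included, only responding survivors remain. The estimate is then s = 80%, which is 4 points too high.

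**Corrected estimate.** Linked survival multiplied by the disability-free proportion among responding survivors is 0.95 × 0.80 = 76.0%. In a simulation of 70,000 patients (the target recruitment), repeated 200 times with d = 5% and 40% non-response, this gave 75.99% and the omission rule gave 73.54%.

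**The case against.** Several points on the other side stand.

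- **Reach.** Only one secondary outcome is structurally affected. The primary outcome, morbidity on day 7, is collected in hospital. The evaluation of PQIP's impact (RQ9) uses outcomes from administrative data, so this defect does not reach it.
- **Direction.** The article does not say how the composite is assembled, and a fuller document not shown may do so. The downward direction depends on linked deaths being kept. Both readings of the printed rule are biased, however, so the rule is wrong for this outcome either way.
- **Size.** Every rate is assumed. The largest figures need high mortality together with high non-response, and nothing in the article says that response differs between hospitals by as much as 20% against 60% non-response.
- **Room for another method.** The assessment of the missingness process is meant to guide the method, and imputation of predictors is offered only as an example. Yet the sentence on missing outcomes is unconditional. The planned comparisons specify no corrected estimate, and under random non-response they would find responding and non-responding survivors alike while the composite stayed biased.

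A reader might infer more than the text supports. Deaths are almost always known, not always, because some patients cannot be linked. The article names a potential for significant loss; it does not predict that many patients will fail to respond. Nor does the argument carry over to change in health-related quality of life. That change is undefined after death, and among surviving non-responders the issue is ordinary, possibly non-random, missingness, which the plan says it will assess.

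**Conclusion.** The concern holds for one-year disability-free survival. Applied as written, the omission rule gives a biased estimate of this secondary outcome even under random non-response among survivors: too low if linked deaths are kept, too high if they are dropped. The size cannot be fixed from the article. Under 5% assumed mortality and 80% of survivors disability-free, the bias is −0.9 to −5.3 points for 20% to 60% non-response, or +4 points under the other reading. With low mortality and good response it is under 1 point.

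This is a stated rule that does not suit a composite from two sources, not a detail left to another document. It should be corrected before disability-free survival is reported or compared between hospitals. It does not threaten the primary outcome, and it does not show that any actual hospital comparison will be materially distorted.

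**What to change.** Add an exception to the Missing data section for disability-free survival:

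- Keep all patients with known vital status, and count linked deaths within one year as failures.
- Handle surviving non-responders by inverse-probability-of-response weighting or by multiple imputation, using baseline and in-hospital data already collected. At its simplest, multiply linked survival by the disability-free proportion among responding survivors.
- Keep the complete-case result as a sensitivity analysis.
- Add a delta-adjusted sensitivity analysis in which surviving non-responders are assumed to be worse than responders with the same characteristics.

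The cost is a change of wording and a little extra analysis, with no new data. The method assumes that disability is missing at random among surviving non-responders; the delta-adjusted analysis probes that assumption.
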